### Procedure

The intervention consists of a 2-week treatment during which TMS will be applied for 10 days over four different brain regions (see below). Since both, short single-region interventions and long multiple-region interventions have achieved positive outcomes in terms of cognitive and functional improvements [e.g., 13, 15, 18, 39] we have followed a cost-effectiveness approach proposing a short (2 weeks) multi-region (four brain areas) intervention to maximize the outcomes while reducing the costs. The stimulation protocol will be the iTBS (600 pulses in bursts of 3 pulses applied at 50 Hz administered every 200 ms -5 Hz- with intervals of 2 s of stimulation and 8 s of rest, lasting 3 min and 12 s). The stimulation will be delivered using a Magstim Super Rapid2 device, with a 70 mm, 8-figure coil and neuronavigated using Brainsight™ 2 device. The stimulation intensity will be set at the 80% of the active motor threshold [see safety guidelines, 10, 34].

Stimulation will be delivered over the DLPFC and the PC in both hemispheres (1 day left DLPFC and right PC with a 15 min interval, and the contralateral areas the following day). The specific target areas for stimulation will be determined individually based on the functional connectivity of each area with two subcortical regions related to AD cognitive dysfunction: the fornix and the hippocampus respectively [40–43]. The seeds used to compute the connectivity analysis, will be 10 mm radius spheres placed bilaterally on the fornix and the hippocampus and adjusted to individual anatomical landmarks. The selection of the specific TMS targets within the DLPFC and PC will be based on its functional connectivity with the seeds. Based on previous literature, the stimulation over the DLPFC is intended to improve participants performance in language tasks and general functioning [11, 13, 14] while stimulation in parietal is intended to improve performance in memory tasks [43, 44].

The placebo condition (sham TMS control group) will be performed using the same stimulation protocol as the active condition over the same areas (bilateral DLPFC and bilateral PC) but with the coil rotated 90° to prevent the magnetic field from inducing electrical activity in the cortex.

Before and after each session, mood and fatigue will be assessed using a visual analogue scale (VAS). At the end of each session, the side effects of TMS will be also assessed.

Along with the TMS treatment, all patients will undergo the CS intervention programme regularly provided by the Consorci Sanitari de Terrassa. The CS is based on Clare and Woods’ definition [45] and Bottino’s et al. model [46], and follows the basic principles of non-pharmacological interventions aiming to improve the quality of life through engagement in significant activities. The program includes 1-h cognitive stimulation and occupational therapy group sessions three times per week (10–12 patients per group). All sessions are conducted by an occupational therapist and supervised by a clinical neuropsychologist who design the CS for each patient. All sessions include reality orientation therapy for 10 min, and training in attention and concentration, memory, language, calculation, gnosias, praxias, or executive function for 50 min [for more details see, 47].

Neuropsychological, functional and emotional aspects will be assessed before and after the intervention (see Table 2 and Fig. 1). A neuropsychologist blinded to the treatment will manage the outcome measurements at all intervention time points.

**Table 2 Tab2:** Outcome measures

*Primary outcome measures*	
Memory	• Logical Memory, Wechsler Memory Scale IV (WMS-IV) [48] • International Shopping List Task • One Card Learning Task of the neurocognitive computerized battery CogState [49, 50]
Attention	• Identification Task of CogState computerized battery [49, 50] • Direct digits of the Wechsler Adult Intelligence Scale IV (WAIS-IV) [51]
Working memory	• Ad hoc computerized Zero and One-Back task and the subtest of the backward digit span test of WAIS-IV [51]
Executive functions	• Five Digit Test [52] • Ad hoc computerized Go/No-Go task • Verbal fluency test (letters P-M-R and animals) [53]
Language	• Token Test [54] • Short form of the Boston Naming Test [55]
Processing speed	• Detection Task of CogState computerized battery [49, 50]
General cognitive	• Alzheimer’s Disease Assessment Scale – cognitive subscale (ADAS-Cog) [56]
*Secondary outcome measures*	
Functional connectivity	• Assessed one time after 10 treatment sessions, through the registry of brain activity in resting state MRI
Functional capacity	• Functional Assessment Questionnaire (FAQ) [57] • UCSD Performance-Based Skills Assessment (UPSA) [58]
Mood changes (depression)	• Hospital Anxiety and Depression scale (HAD) [59] • Geriatric Depression Scale (GDS) [33]
Activities of daily living	• Alzheimer’s Disease Assessment Scale – activities of daily living subscale (ADAS-ADL) [56]
*Modulatory outcome measures*	
Premorbid intellectual level	• “Word Accentuation Test” (a Spanish language test) [60]
Cognitive reserve	• Cognitive Reserve Questionnaire [61]
ApoE (ε4, ε2)	• Genetic analysis

Given the need of multiple administrations, we avoided neuropsychological tests with a marked practice effect, and selected, when possible, tests with parallel versions. The length of each assessment session is ~ 2 h.

All participants will undergo an MRI scan before and after their participation in order to: (1) detect the presence of neurological disorders; (2) localize individual cortical targets for TMS based on their functional involvement in cortico-subcortical networks; (3) guide neuronavigated TMS; and (4) assess the functional and structural brain changes after the intervention.

First exploration, lasting ~ 30 min, will consist in a brain volumetric acquisition (3D) and a resting state acquisition. At the end of the study (three days after treatment), resting state will be acquired again to obtain reliable data on the effects of the intervention on brain activity.

The planning of the clinical trial following the SPIRIT guidelines is displayed in Fig. 1.

**Fig. 1 Fig1:**
[figure not shown]
Trial timeline following SPIRIT recommendations

### Ethical and legal aspects

Patients’ participation will be voluntary after being informed about the objectives of the study and signing an informed consent form. The participants will be free to withdraw from the study at any time. The researchers agree to respect all the established current legislation regarding clinical research (WMA Declaration of Helsinki, 2004; Law 41/2002 on patient autonomy). The Institutional Review Board of the Consorci Sanitari de Terrassa has approved this project.

In accordance with Regulation (EU) 2016/679, on the protection of personal data, any data collected from the participants will be treated with strict confidentiality.

### Possible risks, side effects and discomforts

TMS has been used in research for more than 20 years and safety guidelines have been developed [62]. In this study, all the safety recommendations will be followed and a doctor will always be on call during the TMS sessions.

### Statistical analyses

Statistical analyses will be performed using SPSS (v. 23). We will perform a descriptive analysis of demographic and clinical variables (age, sex, years of schooling, diagnosis, and comorbid disorder) and multivariate analysis of variance for repeated measures of cognitive, emotional and functional variables included as a measure of efficacy. All statistical tests will be performed using a significance level of 0.05.

For processing and analysis of magnetic resonance images we will use different software packages: FSL (FMRIB Software Library, www.fmrib.ox.ac.uk/fsl), and FreeSurfer (http://surfer.nmr.mgh.harvard.edu).

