Willingness to undergo MRI scan	Being under pharmacological treatment with medications indicated in the security TMS guidelines [34]
Signed consent form, previously approved by the Institutional Review Board of the Consorci Sanitari de Terrassa	Drug or alcohol consumption or history of abuse in the 24 months prior to the study
	Implants of metal pieces in the head (excluding dental implants)
	Any of the following medical devices: pacemaker, implanted medication pumps, vagal nerve stimulators, deep cerebral stimulators, transcutaneous electrical stimulation units, ventriculo-peritoneal derivations, titanium plates, cochlear implants, aneurysm clips, etc.

Participants will be selected from patients attending the Dementia Unit at Consorci Sanitari de Terrassa.

To calculate the sample size we used G*Power software (v 3.1.0.2) [35, 36], assuming a dropout risk of a 20% (so the withdrawal of participants does not undermine the clinical relevance of the results), a type I error probability (α) of 0.05, and a type II error probability or statistical power (1 − β) of 0.8. The effect size for a treatment consisting of CS is medium [37] and, given the recent results [5, 19] we expect TMS to increase the effects of CS alone, then assuming a Cohen’s effect size of at least 0.6. Thus, the total recommended sample size is 45, 15 per arm to which we added 3 more participants per group to cover the 20% dropout risk. The risk of clustering effect [38] is absent in this trial since the centre and the healthcare professionals providing the treatments (TMS and/or CS) will be the same for all patients.

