## Limitations

The main limitation of this study is the heterogeneity of AD patients. The variability in clinical symptoms can hinder the capacity to extract robust findings from clinical trials. To avoid this risk, a wide range of inclusion and exclusion criteria have been established. This strategy also comprises another limitation related to the recruitment process to achieve the required sample size. Thus, the strict exclusion criteria will prolong the recruitment process but it will ensure the detection of clinically meaningful effects.

Finally, another major possible limitation will be the experimental mortality due to the length of the study, which includes two follow-up assessments 1, 3, and 6 months after the intervention.

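### The named efficacy analysis, a repeated-measures MANOVA, uses only patients complete at all five assessments unless data are imputed first, although the plan expects 20% dropout

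*Protocol article*

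**What the plan says.** All references are to the protocol article.

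- **Method.** Statistical analyses plans a "multivariate analysis of variance for repeated measures of cognitive, emotional and functional variables included as a measure of efficacy". It does not say whether this is one joint model, one per cognitive domain or one per test.
- **Software and level.** "Statistical analyses will be performed using SPSS (v. 23"), and "All statistical tests will be performed using a significance level of 0.05".
- **Visits.** Outcomes are assessed before treatment (Procedure) and then immediately and 1, 3 and 6 months after it (Abstract), which makes five assessments. Limitations counts two follow-ups but lists the same three months.
- **Outcomes.** Table 2 lists the primary tests in seven cognitive domains, then functional and mood scales as secondary.
- **Sample size.** Under Sample, "the total recommended sample size is 45, 15 per arm", and 3 per arm are added, "assuming a dropout risk of a 20" per cent. This gives 18 per arm, 54 in all.
- **Attrition.** Limitations states that "another major possible limitation will be the experimental mortality due to the length of the study".

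**The concern.** A classical repeated-measures MANOVA works on one complete outcome vector per patient, and the SPSS repeated-measures procedure deletes incomplete cases listwise. A patient who attends everything except the 6-month visit therefore contributes nothing, not even to the immediate post-treatment comparison.

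In a progressive disease, leaving a study plausibly relates to decline. A comparison of completers is then no longer a comparison of the groups as randomised. Recruiting 3 more per arm restores numbers but does not address that bias. Data already collected are also discarded in a small trial.

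A second difficulty depends on how the primary tests are grouped. A joint multivariate model of all of them could have more dimensions than error degrees of freedom.

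**Working it through.** **The plan's own figure.** 15 per arm × 1.2 = 18 per arm, and 3 × 18 = 54, as stated. I take the 15 as given, because the article names neither the test nor the effect-size metric behind it.

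**Complete cases at the planned dropout**
- 54 × 0.8 = 43.2 patients, or 18 × 0.8 = 14.4 per arm. This is below 15, because adding 20% to 15 is not the same as allowing for a 20% loss: 15 / 0.8 = 18.75, so 19 per arm and 57 in all.
- Patients lost: 54 − 43.2 = 10.8. An isolated missing value in a patient who stays would reduce the complete cases further.

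**Data discarded.** Assumption: dropout is spread evenly over the four post-treatment visits, so 10.8 / 4 = 2.7 patients leave before each one.
- Those leaving before the immediate visit have no post-baseline record. The later groups have 1, 2 and 3 records each.
- Patients with an immediate result who are still excluded: 3 × 2.7 = 8.1.
- Records discarded: 2.7 × (0 + 1 + 2 + 3) = 16.2.
- Records observed: 43.2 × 4 + 16.2 = 189.
- Share discarded: 16.2 / 189 = 8.6%.

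**Dimensions.** My count of primary tests in Table 2 is memory 3, attention 2, working memory 2, executive functions 3, language 2, processing speed 1 and general cognition 1, which sums to 14. This is a minimum, since some tests give more than one score. Five assessments give 4 within-patient contrasts. Error degrees of freedom are N − 3.

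| Model | Dimensions | Error df at N = 54 / 45 / 43 | Fully multivariate group-by-time test |
|---|---|---|---|
| One per test | 1 × 4 = 4 | 51 / 42 / 40 | estimable |
| One per domain | at most 3 × 4 = 12 | 51 / 42 / 40 | estimable |
| All 14 tests jointly | 14 × 4 = 56 | 51 / 42 / 40 | not estimable |
| All 14 plus 5 functional and mood scales | 19 × 4 = 76 | 51 / 42 / 40 | not estimable |

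A numerical check of the 56-dimension error matrix gave rank 51 at N = 54 and 42 at N = 45, so it is singular even with no dropout. In that joint model two tests can still be computed: the averaged within-patient test (14 dimensions; error df 51 × 4 = 204 at N = 54, 42 × 4 = 168 at N = 45), which leans on sphericity, and the between-group test (14 dimensions against 51 or 42).

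**Baseline adjustment.** Relative to change from baseline, using baseline as a covariate gives a variance ratio of (1 − r²) / (2(1 − r)) = (1 + r) / 2. That is 0.75 at r = 0.5 and 0.85 at r = 0.7, a reduction of 25% or 15%. The article gives no r, so both values are assumptions.

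**The case against.** The strongest reply is that the article nowhere specifies a complete-case analysis. Listwise deletion belongs to the method and the software. Missing-data handling is commonly left to an analysis plan, which is not shown and may specify imputation. This stands as a condition: the concern applies unless data are imputed first. It does not remove the concern, because the method the article names cannot by itself use an incomplete patient, and the only response to dropout that it gives is over-recruitment.

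Over-recruitment does anticipate most of the loss of precision. What remains is the small shortfall (14.4 against 15 per arm), the discarded records and the possible bias. The size of that bias cannot be computed from the document.

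Three stronger readings are tempting and are not supported:
- *The planned analysis cannot be computed.* A reader might infer this from 56 dimensions against 51 error degrees of freedom. The article does not say that all 14 tests enter one model, and models per domain or per test are estimable. Even a joint model loses only the fully multivariate within-patient tests.
- *All 11 or so dropouts lose an immediate result.* Under even spread about 2.7 leave before that visit, so the figure is about 8.
- *Treating baseline as a repeated measure is an error.* Under randomisation the group-by-time contrast validly estimates the difference in change, so baseline adjustment only gains efficiency. Follow-up contrasts by arm and visit after an omnibus test are likewise routine content of an analysis plan.

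**Conclusion.** The concern holds in conditional form. Followed as written and without prior imputation, the efficacy analysis is a completers' analysis in a trial that expects 20% dropout and itself names attrition as a major possible limitation. The size is about 43 of 54 patients analysed. Under even spread of dropout, about 8 patients with an immediate result are excluded and about 9% of observed post-baseline records are lost. Bias arises if dropout relates to outcome; its direction and size are unknown.

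The dimension problem is real only for a joint model of all primary tests. Splitting by domain or test removes it, but those models remain complete-case.

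**What to change.** Replace the MANOVA with a linear mixed model for repeated measures per endpoint (SPSS MIXED):

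- Outcome: post-baseline scores. Fixed effects: arm, visit, arm-by-visit and baseline score. Unstructured covariance, fitted by REML.
- Include every randomised patient with any post-baseline value, analysed as randomised. Under the even-spread assumption this is 54 − 2.7 = 51.3 patients and all 189 records, against 43.2 patients and 172.8 records. The model relies on dropout being missing at random, and patients with no post-baseline value still drop out of it.
- Report arm contrasts by visit. The article does not designate a primary contrast or visit, so the investigators should choose them in line with the hypothesis in the Introduction, which compares the combined treatment with cognitive stimulation alone.
- State a multiplicity rule across the primary tests. Fourteen separate models each at 0.05 would otherwise give a family-wise error of 1 − 0.95^14 = 51% if the tests were independent.
- Add one missing-not-at-random sensitivity analysis.

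The cost is rewording of the statistical section and a little more analysis work, with no extra data and the same software. Trial status reports that recruitment had not begun, so the change can precede any outcome data.

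### The named efficacy model, a repeated-measures MANOVA, has no baseline covariate; adjusting for each patient's own baseline score would be more precise at almost no cost

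*Protocol article*

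**What the plan says.** The Statistical analyses section of the protocol article gives the efficacy analysis in one sentence: a "multivariate analysis of variance for repeated measures", applied to the efficacy measures in the cognitive, emotional and functional domains. It is to be run in SPSS, and "All statistical tests will be performed using a significance level of 0.05". The section does not list a covariate, the levels of the time factor or the contrast to be read.

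The Procedure section says "Neuropsychological, functional and emotional aspects will be assessed before and after the intervention". The Abstract places the post-treatment assessments immediately after the intervention and at 1, 3 and 6 months. Each efficacy measure therefore has one pre-treatment and four post-treatment values.

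The Sample section assumes an "effect size of at least 0.6" and concludes that "the total recommended sample size is 45, 15 per arm". It then adds three patients per arm for dropout, giving 18 per arm. It gives no SD and no correlation between visits.

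**The concern.** The named model is an analysis of variance. When such a model is fitted to variables measured before and after treatment, the pre-treatment score is ordinarily one level of the repeated factor. The treatment effect against baseline then sits in the group-by-time term, which compares the arms on change from baseline. If the group main effect is read instead, the five-visit average includes a visit at which randomisation makes the true difference zero. Neither form uses the regression of the follow-up score on the baseline score.

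What is at stake is precision. With 15 evaluable patients per arm, chance baseline differences on cognitive tests can be sizeable, and a change score over-corrects for them when the correlation is below 1. The Limitations section names patient heterogeneity as the main limitation, and baseline adjustment addresses part of it with data the trial already collects.

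**Working it through.** **Inputs from the article.** Three arms, 1:1:1; 15 evaluable and 18 randomised per arm; effect size 0.6; level 0.05; one baseline and four follow-ups.

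**Assumptions, not in the article.** Two-sided tests; 0.6 read as a pairwise difference in raw SD units (the article does not say whether it is d or f); equal SDs at all visits; correlation rho between visits, shown as a range.

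**The plan's own figure.** The stated total of 45 for 80% power does not reproduce. A two-sided two-sample t-test with d = 0.6 needs 45 per arm. A one-way ANOVA with three arms needs 30 in total at f = 0.6 and 111 at f = 0.3. There is thus no supported 80% to start from, and the powers below start from 15 per arm.

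**One pre and one post score** (in units of the raw variance):
- Change score: 1 + 1 − 2·rho = 2(1 − rho).
- Baseline-adjusted: 1 − rho².
- Ratio: (1 − rho²)/[2(1 − rho)] = (1 + rho)/2.

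Power is from the noncentral t at 15 per arm, with noncentrality 0.6/√(2V/15), 28 df for the change score and 27 for the adjusted analysis.

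| rho | V change | V adjusted | ratio | saving | power, change | power, adjusted |
|---|---|---|---|---|---|---|
| 0.5 | 1.00 | 0.75 | 0.75 | 25% | 35.5% | 44.8% |
| 0.6 | 0.80 | 0.64 | 0.80 | 20% | 42.6% | 50.8% |
| 0.7 | 0.60 | 0.51 | 0.85 | 15% | 53.5% | 60.2% |
| 0.8 | 0.40 | 0.36 | 0.90 | 10% | 70.8% | 75.2% |

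Outside this range the saving is 35% at rho 0.3 and 5% at rho 0.9. At rho 0.5, 15 per arm work like 15/0.75 = 20.

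These formulas omit the small cost of estimating the slope. With normal baseline scores and a slope pooled over three arms of 15 (42 df), it is about 1/(42 − 2) = 2.5% of the adjusted variance. That trims the gains slightly and cancels them only when rho exceeds about 0.95.

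**Mean of the four follow-ups, equal correlation.** The variance of the mean is (1 + 3·rho)/4. The change from baseline has variance (1 + 3·rho)/4 + 1 − 2·rho, and the adjusted mean has (1 + 3·rho)/4 − rho².
- rho 0.5: 0.625 against 0.375, a saving of 40%.
- rho 0.6: 0.500 against 0.340, a saving of 32%.
- rho 0.7: 0.375 against 0.285, a saving of 24%.
- rho 0.8: 0.250 against 0.210, a saving of 16%.

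**Group main effect over five visits.** A lasting 0.60 SD effect averages to (0 + 4 × 0.60)/5 = 0.48 SD.

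**Separating baseline handling from the form of the test.** A simulation (3,000 replicates, 15 per arm, 0.6 SD in the active arm only, three-arm tests) gave these powers:

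| rho | five-visit group-by-time MANOVA | ANOVA of mean change | ANCOVA of mean follow-up |
|---|---|---|---|
| 0.5 | 29% | 55% | 76% |
| 0.8 | 70% | 91% | 95% |

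Only the step from the second power column to the third is due to the handling of baseline. The step from the first to the second comes from the unstructured multi-degree-of-freedom test.

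**The case against.** The strongest objection is that the article is silent rather than wrong. It never states that baseline is a time level, and it never excludes a covariate. Its one-sentence model also leaves out the modulatory variables in Table 2, so the sentence is plainly not the whole model. Covariate lists are often left to a full protocol or SAP, and none is shown here. This stands in part: baseline as a visit is an inference, if the likely one. It does not dispose of the point, because the article names a model, and that model in its ordinary form has no baseline covariate. A better use of data already collected can be recommended on that basis.

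It is also fair to say that this is a matter of efficiency. In a randomised trial the change-based test is valid. A reader might infer bias or an invalid test, but nothing in the document supports that.

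Three further inferences go too far:
- **The loss applies to every contrast.** It does not. A comparison of 1 month with 6 months does not involve baseline.
- **The group main effect carries a chance baseline difference in full.** Under equal correlation it carries (1 + 4·rho)/5 of it: 0.60 at rho 0.5 and 0.84 at rho 0.8. The article also does not say that this effect will be read.
- **Power may be computed at 18 per arm.** That assumes no dropout, whereas the Sample section says "we added 3 more participants per group to cover the 20% dropout risk", so 15 is the planned evaluable number.

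**Conclusion.** The point holds as a recommendation to improve precision. As named, the efficacy model has no baseline covariate, and in its usual form it would compare arms on change from baseline. Own-baseline adjustment would then lower the variance by 25% to 10% for a single follow-up and by 40% to 16% for the mean of four follow-ups, for rho from 0.5 to 0.8. For a single follow-up at 15 per arm this is worth about 9 points of power at rho 0.5 and about 4 at rho 0.8.

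The size rests on assumptions that the article does not supply: rho, equal variances, equal correlation for the four-visit figures, and 0.6 as a pairwise raw-SD difference. The direction does not depend on the exact rho: the formula favours adjustment for every rho below 1, and the slope-estimation cost matters only very close to 1. Even with adjustment, power in this reading stays below 80% for a single follow-up across rho 0.5 to 0.8, so adjustment does not repair the sample size.

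**What to change.** State in the statistics section that, for each efficacy outcome, the response is the post-treatment visits only and the patient's own baseline score on that instrument is a covariate, with a baseline-by-visit term if a longitudinal model is used. Report the baseline-adjusted difference between arms with its 95% CI. If the authors already intend this, one sentence saying so settles the point.

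The cost is that sentence and one or a few degrees of freedom per outcome. No new data or visits are needed. The Trial status section says recruitment has not begun, so the choice can be fixed before any outcome is seen.
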